## Abstract

**Background:**

Uganda is experiencing a shift in major causes of death with cases of stroke, heart attack, and heart failure reportedly on the rise. In a study in Mukono and Buikwe in Uganda, more than one in four adults were reportedly hypertensive. Moreover, very few (36.5%) reported to have ever had a blood pressure measurement. The rising burden of CVD is compounded by a lack of integrated primary health care for early detection and treatment of people with increased risk. Many people have less access to effective and equitable health care services which respond to their needs. Capacity gaps in human resources, equipment, and drug supply, and laboratory capabilities are evident. Prevention of risk factors for CVD and provision of effective and affordable treatment to those who require it prevent disability and death and improve quality of life. The aim of this study is to improve health profiles for people with intermediate and high risk factors for CVD at the community and health facility levels. The implementation process and effectiveness of interventions will be evaluated.

**Methods:**

The overall study is a type 2-hybrid stepped-wedge (SW) design. The design employs mixed methods evaluations with incremental execution and adaptation. Sequential crossover take place from control to intervention until all are exposed. The study will take place in Mukono and Buikwe districts in Uganda, home to more than 1,000,000 people at the community and primary healthcare facility levels. The study evaluation will be guided by; 1) RE-AIM an evaluation framework and 2) the CFIR a determinant framework. The primary outcomes are implementation – acceptability, adoption, appropriateness, feasibility, fidelity, implementation cost, coverage, and sustainability.

**Discussion:**

The study is envisioned to provide important insight into barriers and facilitators of scaling up CVD prevention in a low income context.

This project is registered at the ISRCTN Registry with number ISRCTN15848572.

The trial was first registered on 03/01/2019.

## Background

### Cardiovascular disease and risk factors on the rise

Globally, approximately one third of all deaths are attributed to cardiovascular disease (CVD) [1]. In Europe, CVD are estimated to be responsible for half of all deaths causing more deaths than any other condition [2]. Approximately, three quarters of all estimated global deaths due to CVD take place in low and middle income countries (LMICs) [3]. Moreover, it is projected that by the year 2030, CVD alone will be responsible for more deaths than infectious diseases (including HIV/AIDS, tuberculosis, and malaria), maternal and perinatal conditions, and nutritional disorders combined in LMICs [4]. The high and increasing burden of CVD in developing countries is attributable to urbanization and higher levels of risk factors, low age of manifestation, large population sizes and the high proportion of young adults [3]. The eight modifiable risk factors including: history of hypertension or diabetes, obesity, unhealthy diet, lack of physical activity, excessive alcohol consumption, raised blood lipids and psychosocial factors are equally on the rise especially in LMICs [5]. The main CVD causing most death are heart failure, stroke, coronary heart disease as well as renal complications.

Sub-Saharan Africa (SSA) is experiencing a rapid epidemiological transition [3] and Uganda in particular has seen major causes of death shift from exclusively infectious diseases to a combination of communicable and non-communicable diseases (NCDs) [6]. The first nationwide NCD risk factor survey reported a prevalence of hypertension of 26.4%; 28.9% in urban and 25.8% in rural areas, among whom only 7.7% were aware of their high blood pressure status [7]. Authors allude that low awareness mirror a high burden of undiagnosed and un-controlled high blood pressure in the population [7]. In a study in central region focusing on Mukono and Buikwe districts, more than one in four adults were reportedly hypertensive [8]. Moreover, very few (36.5%) reported to have ever had a blood pressure measurement [8]. In the same districts, a trend analysis of health facility data revealed increasing burden of CVD at these facilities with cases of ischemic, rheumatic and chronic heart diseases reportedly on the rise. Likewise, stroke, hypertension and diabetes mellitus are on the rise [9].

### Preparedness of the healthcare system

The burden of CVD in LMICs is compounded by a lack of integrated primary health care programs for early detection and treatment of people with increased risk. As a result many people in LMICs who suffer from CVD have less access to effective and equitable health care services which respond to their needs [10]. Consequently, many individuals are detected late in the course of the disease and die younger from CVD, often in their most productive years. At the household level, emerging evidence suggest that CVD are contributing to poverty due to catastrophic health spending and high out-of-pocket expenditure [10]. At the macro-economic level, significant proportions of national health budgets for LMICs are directed towards managing CVD. Moreover, managing these conditions is a daunting task in LMICs [10]. High burden of disease, socioeconomic barriers and inequalities in access to treatment, suboptimal staffing including shortage of physicians at health-care facilities and limited capacity to conduct investigations are widely documented as limiting factors [11–15].

In Uganda, the healthcare system is oriented to manage communicable diseases and this has not changed significantly even with the changing trends in NCDs [16]. A 2013 NCD needs assessment found that none of the health facilities in Uganda met the World Health Organization (WHO) standard for essential tools and medicines needed to implement effective NCD interventions [17]. Moreover, capacity gaps in human resources, equipment, drug supply, and laboratory capabilities were evident [17].

In Mukono and Buikwe districts, an assessment of the health system capacity to care and manage hypertension cases revealed a multitude of gaps both from the health provider and patient perspectives. The health workers highlighted that they had inadequate skills to manage hypertension and its complications, lacked relevant guidelines and equipment, were understaffed and the health facilities they worked in frequently suffered stock outs of antihypertensive [18]. The health workers also reportedly noted that high costs, adherence challenges, and transport problems affected patients uptake of hypertensive services [18].

### Interventions, strategies and models

Combination prevention of risk factors for CVD and provision of effective and affordable treatment to those who require it prevent disability and death and improve quality of life. In the current study, we are drawing lessons from the HIV response in combination with the Innovative Care for Chronic Conditions (ICCC) framework to implement contextually appropriate interventions that address prevention of CVD in Mukono and Buikwe districts in Uganda. The ICCC framework is an adaptation of the chronic care model (CCM) but has mainly been tested in high income countries [19]. The framework expands the policy environment and puts more emphasis on the role of the community, to enable its applicability in a low income context [20]. A combination of both HIV/AIDS response models which enjoy extensive application in SSA and the ICCC framework provide synergies for a comprehensive study on CVD prevention in a low income setting.

### Evidence for the proposed interventions, strategies and models

Innovative HIV/AIDS response strategies have prevented 8 million deaths and 30 million new infections since 2000, and many of the worst-affected countries have managed to cease—and in some cases, reverse—the spread of the disease [21]. In SSA, a steady reduction in HIV incidence and AIDS-related deaths is clearly documented [22]. Although the fight against HIV/AIDS is not over and remains an important priority, the HIV/AIDS response model provides unprecedented evidence that chronic care in LMICs is feasible amidst scarce resources. Successful HIV models [23] responsible for the celebrated milestones in SSA have been tested in several countries including Tanzania, South Africa, Zambia, Uganda, and Malawi [22]. As reported by Olmen and colleagues, the innovative responses are an interplay of three pillars: a public health approach (PHA); community and peer support; and strengthening the health services in which care is embedded [22]. The main principles of the PHA are simplification of treatment protocols and clinical monitoring; decentralization of ART care delivery to the local health centre and community level; and task shifting and involvement of community and people living with HIV (PLWHA) in program design, management, and care [22]. In the current project, we will borrow from these models to implement a comprehensive package for prevention of CVD. At the community, we train community health workers (locally referred to as Village Health Teams (VHTs) to conduct health education, risk assessments, and motivational interviewing; facilitate creation of or support strengthening of community networks; and promote cardiovascular health and education. At the primary healthcare level, we shall identify and train non-physicians (mainly clinical officers/nursing staff) to screen for risk factors and provide basic care and management of CVD risk factors; train peers counsellors to support patient follow-up, conduct peer counselling and risk assessment; and provide basic buffer supplies to ensure continuity of CVD prevention and control services at the level. We integrate a mobile and e-health component to improve data capture, storage and patient follow-up.

## Study objectives and research questions

### General objective

The general objective of the study is to implement an enhanced CVD prevention program and evaluate the implementation process and determine the effectiveness on improving profiles for people with intermediate and high risk factors for CVD at the community and health facility levels.

### Research questions

How effective is an enhanced community approach in improving population knowledge and screening for CVD risk factors, referral and enhancing lifestyle change in a real world setting versus usual care? What is the uptake and what factors influence implementation?How effective is an enhanced primary healthcare approach in improving CVD risk profiles of patients attending healthcare facilities? What is the uptake in routine practice and what factors influence implementation?What is the utility of an e-health screening tool in profiling for CVD risk factors at the community and at primary healthcare level? What is the uptake and what factors influence implementation uptake?What is the impact of an enhanced comprehensive CVD prevention program on patient outcomes versus usual care?

## Methods/design

### Study design

The overall study is a type 2-hybrid stepped-wedge (SW) design that emphasizes both clinical effectiveness and implementation outcomes, with the eventual goal of more rapid translation and uptake to usual care settings. The design employs mixed methods with iterative improvement cycles [24]; and data collection entailing repeated measures at the community, household, health facility and patient levels. The proposed design involve incremental execution and adaptation and allows continued measurement of key process and outcome indicators [24]. Sequential crossover take place from control to intervention until all clusters are exposed (Fig. 1). The core analyses will be qualitative and we will feed quantitative data into these to further our understanding.

**Fig. 1 Fig1:**
[figure not shown]
Illustration of a stepped-wedge study design with periodic surveys every 6 months

### Context, study sites and sequencing

The study will take place in Mukono and Buikwe districts, home to more than 1,000,000 people. The two districts are largely rural with a significant proportion (25%) living in urban or semi-urban neighbourhoods. The districts share common boarders and lie along the main transport corridor connecting Kampala (the capital city) through Nairobi to Mombasa Sea Port in Kenya. The districts are strategically located between the two biggest urban areas of Jinja and Kampala. The prevalence of hypertension is high in these districts and only 35.6% of the adult general population have ever had their blood pressure measured. More than one in four of the general adult population are hypertensive [25] and yet the health system is very weak to adequately care for them [26]. This context provides an opportunity to scale-up proven, safe, efficient and cost-effective interventions to mitigate CVD risk factors. Mukono and Buikwe districts together have 7 health sub districts, and 23 sub-counties (15 in Mukono and 8 in Buikwe). Regarding health facilities, the two districts have more than 126 health facilities of which 40.5% are government owned, 41.3% are private for profit (PFP) and the rest are private not for profit (PNFPs). Of the facilities, 5 are hospitals (1 public), 4 health Centre IVs (3 public) and 23 are HCIIIs (20 public). For this study, 20 parishes (Fig. 2) hosting the 20 public health centre IIIs in Mukono and Buikwe will be included. From each Parish, the HCIII is enrolled for the Health facility study and four randomly selected villages are enrolled for the community study. In the stepped wedge, five parishes are initially assigned to the intervention (cycle 1) and the rest in usual standard of care (control). Every 6 months, additional five parishes (health facilities and villages) are switched to intervention till all are exposed at the end of the 4 cycles. We include Kawolo Hospital in Buikwe and Kojja and Mukono HCIVs in Mukono to provide a referral mechanism for complicated cases. Minimal support including training is provided to these levels by the project.

**Fig. 2 Fig2:**
[figure not shown]
Map of Mukono and Buikwe showing selected parishes for the stepped wedge study

### Description of formative activities, and intervention plans

From October 2017, the study team conducted a situational analysis of the CVD burden and contextual factors in Uganda with a focus on Mukono and Buikwe districts. The study revealed gaps (reported earlier) and a range of contextual recommendations to improve CVD prevention. The recommendations from the analysis are summarized as follows: empower lower level health facilities to manage CVD and risk factors, utilize volunteers in screening for CVD using non-laboratory means, utilize expert clients in health promotion activities and peer support, institutionalize peer model for care and management and improve data capture for CVD and create database.

Drawing from the recommendations and in the context of global literature on best practices (reported earlier), we propose to advance CVD prevention along the cascade through health promotion and education and screening for risk factors at the community (community plan) and strengthen health services at the primary healthcare level (Primary healthcare plan) in Mukono and Buikwe district in Uganda. This study is part of a bigger project code named “SPICES”. SPICES is an acronym for Scaling up Packages of Interventions for Cardiovascular disease prevention in selected sites in Europe and sub-Saharan Africa. The partners implementing SPICES and their respective countries are: University of Antwerp, Belgium (Coordinator); Brighton and Sussex Medical School and Nottingham Trent University, both in the United Kingdom; Brest University in France, and the University of Limpopo in South Africa.

### Primary healthcare plan

Facilities in the intervention cycle(s) are strengthened with certain aspects to improve screening, diagnosis and management of risk factors for CVD. These aspects include: supplies and equipment such as blood pressure (BP) monitoring devices, glucometers and buffer stock for first line anti-hypertensive medicines; guidelines and standardized treatment protocols; computers and digital devices to improve data capture and storage; and training health workers and patients peers. Health workers are trained based on a manual adopted with modification from the Uganda Ministry of Health training manuals and others materials on Non communicable diseases. Trained health workers are equipped with a simplified algorithm (adopted with modification from the hearts and the WHO PEN protocols and the Uganda Clinical guidelines) to guide them in screening, diagnosis and managing the risk factors. Meanwhile, peers are equipped with knowledge and skills to conduct peer counselling, support screening activities and follow-up of patients.

### Community plan

The community plan revolves around working with community health workers (VHTs), existing networks and community structures to promote knowledge, improved lifestyles, risk assessment and cardiovascular health. CHWs are trained to conduct health education, promote lifestyle change through motivational interviewing and goal setting techniques, screen for risk factors at the community using non laboratory tools, and conduct home to home visits. Existing community networks and community structures are identified and supported to promote improved lifestyle behaviours, screening for risk factors and cardiovascular health education and promotion. Electronic and print media (messages) are circulated to enhance health promotion and improved lifestyle behaviours.

### Data capture and information management

To enhance data capture and information management and storage, both the community and health facility plans are supported with an e-health and mobile health platforms. The electronic plan will be explored to understand its contribution in improving data management and screening for CVD risk factors, enhancing linkage and referral as well as triggering behaviour change. Electronic enhancement entail mounting data capture and screening tools on a mobile/computer platform and used for registration, risk assessment and where possible linking/confirming linkage of participants for service.

### Evaluation plan

To evaluate the study, we propose to conduct a series of cross-sectional surveys every 6 months at time (T) 0, T6, T12, T18 and T24 at the community and health facility levels. We assess with key community and household members, health facilities, health workers, and patients. The evaluations uses both: qualitative assessments – to evaluate the process, barriers and opportunities; and quantitative measurements – to assess effects and process outcomes. During the interventions, formative processes (process evaluations) and detailed documentation of process, costs and activities take place.

### Inclusion and exclusion

#### Inclusion

Both male and femaleAged 18 years and aboveConsent to participate in the study

#### Exclusion

The mentally ill will not be included in the evaluationsNon consenting adults

### Sample size and sampling

#### Community quantitative surveys

For the community series of cross sectional surveys, we adopt the formula by Hemming et al. 2016 for cross sectional sample size determination for a stepped wedge study. To determine a moderate effect size of 0.3 (SD 1) for say change in Blood pressure at 5% significance, and detectable power of 88%, before and after the exposure to the intervention, given a sample size that is feasible and realistic in these setting, with four (4) steps and five (5) clusters per step, a total sample size of 50 participants per cluster is assumed reasonable [27]. However, assuming an intracluster correlation coefficient, r, of 0.01, a fixed cluster sample size, m = 50, survey rounds, t = 5 and a design effect of 2.93 [27] with 20 predetermined clusters; the required total sample size per survey round is 2930 households. We recognise that a random sample of household in a vast geographic setting can return a lot of non-responses. Thus, to cater for non-responding households and to avoid replacement of randomly selected eligible households, we factor in a non-response of 30% and generate the final household sample of 4000; with each cluster contributing 200 households. *Sampling households and participants*: The sampling frame for the surveys is generated through a mapping and listing exercise. All households in the catchment area are assigned a unique number to generate a sampling frame. A random sample of 200 eligible households with at least one adult per household is generated from the sampling frame using a random number generator. The selection is conducted by the study statistician. Study personnel (trained research assistants) approach the selected households for recruitment into the household/community survey. When a selected household is approached and has at least one eligible adult, study personnel describe the purpose of the study in the appropriate language, obtain participant consent and administer the study questionnaire and conduct anthropometric and blood pressure measurements using standardised and validated equipment. All eligible adults in the household aged 25–70 years are enrolled.

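### The stated 88% power for 0.3 SD does not describe the planned community survey, and neither the design effect of 2.93 nor the 2,930 per round follows from the stated inputs

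*Protocol article*

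**What the plan says.** All the figures are in the protocol article, under Sample size and sampling, Community quantitative surveys.

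- Target: "To determine a moderate effect size of 0.3 (SD 1) for say change in Blood pressure at 5% significance", with "detectable power of 88" per cent, "with four (4) steps and five (5) clusters per step".
- Cluster size: "a total sample size of 50 participants per cluster is assumed reasonable".
- The text then turns with a 'however', assumes an ICC of 0.01, and gives "a fixed cluster sample size, m = 50, survey rounds, t = 5 and a design effect of 2.93" with 20 clusters.
- Result: "the required total sample size per survey round is 2930 households".
- A 30% allowance for non-response brings this to 4,000 households per round, 200 per cluster.

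The Evaluation plan has five cross-sectional rounds (months 0, 6, 12, 18 and 24). The Data analysis section fits a random cluster effect and a fixed effect for each step. No power is given for 2,930 or 4,000 households per round.

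**The concern.** The paragraph gives a power and a cluster size as if they belonged together, then multiplies that cluster size by a design effect without restating the power. If the 88% already came from a stepped-wedge calculation, the design is paid for twice. If it did not, it is unclear what it describes. The unit of time shifts as well: a stepped-wedge design effect of this kind gives a total over all rounds, but the product is labelled as the need in each round. Finally, the design effect and the ICC stand side by side as a matched pair and can be checked against each other.

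At stake is whether a reader can tell which effect the survey can detect. A very small but statistically significant change in blood pressure could be judged against a 0.3 SD target that the planned sample far exceeds.

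**Working it through.** **Inputs.** Effect δ = 0.3, SD 1, 5% significance (two-sided assumed), power 88%, N = 20 clusters in four groups of five, T = 5 rounds, ICC ρ = 0.01, m people per cluster per round. The model is the one in the Data analysis section, with constant within-cluster correlation unless stated.

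**1. Variance of the treatment effect (Hussey–Hughes).** With σ² = (1 − ρ)/m and τ² = ρ:

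Var = Nσ²(σ² + Tτ²) / [(NU − W)σ² + (U² + NTU − TW − NV)τ²]

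For this design:
- U = 5 × (4 + 3 + 2 + 1) = 50
- W = 0² + 5² + 10² + 15² + 20² = 750
- V = 5 × (16 + 9 + 4 + 1) = 150

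So NU − W = 250, and the second bracket is 2,500 + 5,000 − 3,750 − 3,000 = 750.

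**2. Reproducing the 88%.** Read 50 as the total over five rounds, so m = 10 and σ² = 0.099:

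Var = 20 × 0.099 × 0.149 / (24.75 + 7.5) = 0.00915, SE 0.0956, power = Φ(0.3/0.0956 − 1.96) = 88.0%.

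This matches the plan. With ICC 0 the same sample would give 91.8%, so the stated 88% already includes clustering.

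**3. The other reading of 50.** With m = 50 per round, σ² = 0.0198:

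Var = 20 × 0.0198 × 0.0698 / (4.95 + 7.5) = 0.00222, SE 0.0471, power above 99.9%.

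The 88% does not belong to this reading even before any inflation.

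**4. What the design effect should multiply.** The individually randomised total is 4 × (1.960 + 1.175)² / 0.3² ≈ 437. For k steps, one baseline round and one round per step:

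DE = {[1 + ρ(km + m − 1)] / [1 + ρ(km/2 + m − 1)]} × 3(1 − ρ)(k + 1) / [2(k − 1/k)]

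| m per round | ICC | k | DE | 437 × DE, all rounds |
|---|---|---|---|---|
| 10 | 0.01 | 4 | (1.49/1.29) × 1.98 = 2.29 | about 1,000 |
| 50 | 0.01 | 4 | (3.49/2.49) × 1.98 = 2.78 | about 1,210 |
| 2.93 as stated | – | – | 2.93 | about 1,280 |

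The first row gives back 20 × 50 = 1,000, which confirms step 2: on that reading the 1,000 is already an inflated, all-round total.

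**5. What the plan did.** 20 × 50 × 2.93 = 2,930, called a per-round requirement. Over five rounds that is 14,650, against about 1,000 to 1,280 needed for the stated target.

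**6. Does 2.93 fit the inputs?** At m = 50 and ICC 0.01 the formula gives 2.78 with k = 4 and 2.70 with k = 5. The parallel-design form 1 + (m − 1)ρ gives 1.49. At m = 50, values near 2.93 appear at ICC about 0.0185 or 0.10 (k = 4), or at 0.05 (k = 5).

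**7. Power of the sample that will be fielded.** 200 × 0.7 = 140 responding households per cluster per round, or 14,000 over the trial; this is slightly below the 2,930/20 = 146.5 in the text. Taking one adult per household:

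| ICC | Cluster autocorrelation (assumed) | Power for 0.3 SD | Effect detectable with 88% power |
|---|---|---|---|
| 0.01 | 1 | >99.9% | 0.09 SD |
| 0.01 | 0.8 | >99.9% | 0.10 SD |
| 0.01 | 0.5 | >99.9% | 0.11 SD |
| 0.10 (assumed) | 0.8 | 99.9% | 0.18 SD |
| 0.10 (assumed) | 0.5 | 95.6% | 0.26 SD |

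**The case against.** **The error is on the safe side.** This stands. Power for 0.3 SD stays above 95% in every scenario run, and no estimate or test is biased. Blood pressure is offered only as an example, effectiveness is the secondary outcome, and the Study design section says the core analyses will be qualitative. That limits the severity but does not make the figures right. The text calls 2,930 required and makes a separate allowance for non-response; it does not present the excess as a deliberate margin.

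**The number 50 is ambiguous.** This also stands. The paragraph first calls it a total per cluster, then a fixed cluster size m beside t = 5 rounds. A reader might infer that 50 per cluster certainly delivers 88%. That holds only if 50 is the total over all rounds, which is the sole reading that reproduces 88%. The conclusion does not need it, because on the per-round reading 88% is wrong too.

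**The source of 2.93.** A reader might infer that the authors used ICC 0.10. The documents do not support this: several combinations of ICC and k give about 2.93, and the cited methods paper is not at hand. The gap between 2.78 and 2.93 is only about 5%. What can be said is that 2.93 does not follow from the ICC and m printed beside it.

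**Conclusion.** The concern holds, as something that should be fixed in the sample-size text for a secondary outcome. Under neither reading of 50 is 88% the power of the planned survey. Multiplying 20 × 50 by 2.93 does not yield a per-round requirement, and 2.93 does not agree with ICC 0.01 and m = 50. The planned 14,000 responding households over five rounds (14,650 by the text's own 2,930) are roughly 11 to 14 times the 1,000 to 1,280 observations that the stated target needs.

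It would be wrong to conclude that the trial is underpowered, or that its primary implementation results are affected. It would also be wrong to fix the detectable effect at 0.09 SD: that value rests on ICC 0.01, constant cluster correlation and one adult per household. Less favourable assumed values take it to about 0.26 SD. The plan enrols all eligible adults in a household, which raises the count of individuals and adds household clustering that the calculation does not contain.

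**What to change.** 1. Say whether 50 is per cluster per round or per cluster over all five rounds.
2. Remove the multiplication by the design effect as the derivation of a required 2,930 per round. If a design effect is shown, apply it to the individually randomised total and label the result as the total over all rounds.
3. Make the design effect agree with the stated ICC (2.78 at ICC 0.01, m = 50 per round, four steps), or state the ICC that was actually used.
4. Since removing the multiplication removes the only derivation of 4,000, present 200 households per cluster as a feasibility choice and give its real power. With about 140 responding households per cluster per round, ICC 0.01 and one adult per household, that is above 99.9% for 0.3 SD, and 88% for about 0.09 SD (0.10 to 0.11 SD at assumed cluster autocorrelation 0.8 to 0.5).
5. Add a sensitivity range for larger ICCs, for example 0.18 to 0.26 SD at assumed ICC 0.10 and autocorrelation 0.8 to 0.5, and note the effect of enrolling all eligible adults in a household.

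The cost is a rewritten paragraph and a short calculation. The field sample need not change.

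### The community survey requirement is calculated in participants, labelled as households without conversion, and then recruited by enrolling every eligible adult in each household

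*Protocol article*

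**What the plan says.** All of this stands in the protocol article under Sample size and sampling, Community quantitative surveys.

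- The target is set for a blood pressure type of outcome: "To determine a moderate effect size of 0.3 (SD 1) for say change in Blood pressure at 5% significance", with "detectable power of 88"%.
- The layout is "with four (4) steps and five (5) clusters per step", with five survey rounds.
- The cluster size is given in people: "a total sample size of 50 participants per cluster is assumed reasonable".
- The adjustment follows: "assuming an intracluster correlation coefficient, r, of 0.01, a fixed cluster sample size, m = 50", and a design effect of 2.93 with 20 clusters.
- The result is given in a different unit: "the required total sample size per survey round is 2930 households".
- A 30% allowance for non-responding households then leads to 4000 households, 200 per cluster.
- The recruitment rule is: "All eligible adults in the household aged 25–70 years are enrolled".

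The section gives no mean number of eligible adults per household, no conversion from participants to households, and no rule that one adult is taken per household.

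**The concern.** The calculation starts with people and ends with households, with nothing in between. The two counts would agree only if each household supplied one participant, and the recruitment rule does not provide for that: it takes all eligible adults, and one adult is only the minimum for a household to be selected.

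The figure governs five survey rounds. Read against 2930 households, a round with 2800 responding households is short. Read against 2930 participants, the unit of the inputs, the same round is over target as soon as households average slightly more than one eligible adult. Any power quoted later could refer to either sample. Adults of one household also tend to resemble each other, so extra people from the same household do not each add a full unit of information.

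**Working it through.** **Inputs from the protocol article:** effect 0.3 SD; 5% significance (sidedness not stated, two-sided assumed); power 88%; 20 clusters in 4 steps of 5; 5 rounds; ICC 0.01; m = 50 participants; design effect 2.93; 30% non-response; 4000 households. **Not in the document, so assumed:** eligible adults per household h, shown from 1 to 2.5; within-household correlation, 0.1 to 0.3.

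**1. Reproducing the stated figure.** 50 participants x 20 clusters = 1000 participants. 1000 x 2.93 = 2930 participants. The number is reproduced exactly; the household label does not follow from it.

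**2. Responding households.** 4000 x 0.70 = 2800. (2930 / 0.70 = 4186 and 2930 x 1.30 = 3809; the stated 4000 is a rounded 20 x 200 between the two.)

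**3. People measured per round = 2800 x h.**

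| Mean eligible adults per household (assumed) | People per round | Relative to 2930 |
|---|---|---|
| 1.0 | 2800 | 96% |
| 1.5 | 4200 | 143% |
| 2.0 | 5600 | 191% |
| 2.5 | 7000 | 239% |

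Break-even: 2930 / 2800 = 1.05 adults per household.

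**4. Discount for household correlation.** Effective number = 2800h / [1 + (h - 1) x household correlation], treating households as equal in size. With h = 1.5 and correlation 0.3: 4200 / 1.15 = 3652. With h = 2.5 and correlation 0.1: 7000 / 1.15 = 6087.

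**5. Does 2930 become right if it is relabelled as participants?** I used the Hussey-Hughes variance for a cross-sectional stepped wedge, with all clusters in control at the first round and five crossing over before each later round. Let s = (1 - 0.01)/m, with m participants per cluster per round, and t = 0.01. The exposure sums are U = 5 x (4+3+2+1) = 50, W = 0 + 25 + 100 + 225 + 400 = 750 and V = 5 x (16+9+4+1) = 150. Then

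variance = 20s(s + 5t) / [(20U - W)s + (U² + 100U - 5W - 20V)t] = 20s(s + 0.05) / (250s + 7.5).

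- m = 10 per round (50 per cluster in total): s = 0.099; variance = 0.29502 / 32.25 = 0.009148; SE = 0.09564; 0.3/SE - 1.96 = 1.177; power = 88.03%.
- m = 50 per round: s = 0.0198; variance = 0.02764 / 12.45 = 0.002220; SE = 0.04712; 0.3/SE - 1.96 = 4.41; power above 99.9%.

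The stated 88% is thus matched by 50 participants per cluster over the whole trial, 1000 in all. This agrees with the article's own word for the 50, a total. The match already includes clustering: with ICC 0 and m = 10, the variance is 20 x 0.1 / 250 = 0.008 and power would be 91.8%. As a cross-check, an individually randomised comparison needs 219 per arm, 438 in all. The design effect at m = 10 is 0.009148 / (4/1000) = 2.287, and 438 x 2.287 = 1002. So 1000 is the figure after the design effect, and multiplying it by 2.93 per round appears to count clustering a second time.

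**The case against.** The best defence is that this is a labelling slip with no harm to the trial. The operational target is explicit: 4000 households approached, 200 per cluster. Counting each household as at least one participant is cautious. Under the stated inputs, power is ample for every headcount in the table. The sizing supports a secondary outcome, and the Study design section describes the core analyses as qualitative. The article is also condensed, so the mean number of adults per household and a household allowance may stand in a fuller document.

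Much of this stands. No bias or loss of power is shown, and the absence of those household details is not in itself a fault. What does not fall away is that the article prints a complete calculation whose result carries a unit its inputs do not support, next to a recruitment rule that prevents the two units from being equated.

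A reader might go further and infer that the survey enrols far more people than it needs by its own figure of 2930, or that a definite number of household visits could be saved. The document does not support either. It gives no number of adults per household, and at exactly one the plan is 4% short. The count of eligible adults is itself unsettled, because the Inclusion section says 18 and above while the sampling text says 25 to 70. Visit savings would rest on the same unknown, on an unsourced household correlation and on 2930 being right.

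**Conclusion.** The point holds in this form: the per-round requirement is derived in participants, stated in households without conversion, and recruited in households from which all eligible adults are enrolled. That needs no outside figure.

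The size of the mismatch depends on the unknown mean number of eligible adults: from 4% below 2930 at one adult to 43% to 139% above it at an assumed 1.5 to 2.5, or about 25% to 108% above after a household correlation of 0.1 to 0.3. An excess is likely but not established.

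A second reading to avoid is that writing participants in place of households would settle the matter. With the stated inputs and a two-sided 5% test, 88% power corresponds to 10 participants per cluster per round, so 2930 per round does not match the stated power in either unit. This rests on the Hussey-Hughes model; the source cited for 2.93 was not available, so the double use of the design effect is the probable explanation and not a proven one.

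**What to change.** 1. State the requirement in participants, and say whether it is per round or over all five rounds.
2. Recompute it in the same edit and do not carry 2930 over. Show how 2.93 is obtained and what it multiplies. If the larger survey is wanted for other outcomes or smaller effects, say so and give the power for those.
3. Add the household step: households to approach = participants x [1 + (h - 1) x household correlation] / h / 0.70. Take h and the household correlation from the baseline survey, which the article reports as under way, and use one age range for eligible adults.
4. Restate the household target per cluster and the power that the enrolled sample gives.

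The cost is a short recalculation from baseline data and a change of wording. No extra participants are needed under the stated inputs. The downside is that published figures change after the baseline round, so the change should be dated and explained.
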